# Therapeutic Improvement in People With Schizophrenia Undergoing tACS/CBTp (Transcranial Alternating Current Stimulation/Cognitive Behavioral Therapy for Psychosis) Associated With Usual Medication Regimen: Protocol for a Pilot, Randomized, Single-Blind Trial

**DOI:** 10.2196/80593

**Published:** 2026-02-10

**Keywords:** schizophrenia, tACS, transcranial alternating current stimulation, CBTp, cognitive behavioral therapy for psychosis, EEG, electroencephalogram, heart rate variability, gender, clinical or functional improvement

## Abstract

**Background:**

Transcranial alternating current stimulation (tACS) applies a low-intensity sinusoidal electrical current through electrodes placed on the scalp to boost the brain’s own oscillation by way of entrainment. When a single frequency is applied, this exogenous oscillation synchronizes with the brain’s endogenous frequency. Gamma frequency synchrony stands out as a binding mechanism for integrating disparate brain networks, mediating perception, cognition, and memory, typically disturbed in schizophrenia. The treatment of schizophrenia includes medication and cognitive behavioral therapy for psychosis (CBTp). We are adding tACS to these usual treatments, targeting gamma oscillation stimulation, to augment the CBTp efficacy in people living with schizophrenia.

**Objective:**

This study aims to elicit cognitive readiness and therapeutic engagement by adding tACS to each CBTp session in individuals with schizophrenia taking their usual medication, to evaluate the possible improvement of the level of functioning, and to determine if the response to intervention is gender specific.

**Methods:**

This is a pilot, prospective, randomized, repeated-measures, single-blind study design. We expect to enroll 28 participants randomly assigned to one of two treatment arms: arm 1 (tACS/CBTp, n=14) or arm 2 (sham tACS/CBTp, n=14; tACS is sham, but CBTp is active). The intervention with active or sham tACS/CBTp will take place weekly for 16 weeks. Primary outcome measures—electroencephalogram, Positive and Negative Syndrome Scale, 16-item Negative Symptom Assessment, and Cognitive Flexibility Scale—will evaluate the efficacy of treatment at the end of the intervention and at the two follow-ups. We will use SPSS (version 29, IBM Corp); the main tests will include repeated measures and mixed design ANOVA.

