tACS, the focus of our study, applies a low-intensity sinusoidal electrical current to the brain through electrodes placed on the scalp, and it is thought to boost the brain’s own oscillation by way of entrainment. When a single frequency is applied, this exogenous oscillation will synchronize with the brain’s endogenous frequency. Conversely, multiple frequencies lead to desynchronization of cortical oscillations [24]. The value of the frequency applied thus becomes a determining factor in the effects sought and identified in tACS studies.

Research focusing on tACS mechanisms has shown that effects result from manipulating the membrane potential of neurons that are aligned with the introduced electric field, mostly pyramidal cells in layer V [25,26]. Upon stimulation by tACS, which will cause an alternating change in membrane potential, these cells demonstrate a resonance specific to the frequency of stimulation, with long-term aftereffects—70 minutes after one stimulation session for 20 minutes [19]—and implications on oscillatory cortical connectivity between different cortical regions [27]. In auditory hallucinations, research has demonstrated interhemispheric miscommunication, where tACS can manipulate auditory perception in healthy participants by decoupling this interhemispheric connectivity [28]. The advantage of using tACS over other noninvasive brain stimulation modalities lies in its effectiveness in entraining endogenous brain oscillations, as it mimics the alternating nature of these oscillations [29,30].

From a practical standpoint, tACS exhibits superior cost, portability, tolerability, and safety profiles [17]. tACS is a feasible tool that reshapes or resynchronizes intrinsic brain rhythms, manipulating the associated brain functions without adding extra excitatory or inhibitory burden.

We hypothesize that tACS targeting gamma oscillations, added to each CBTp session, will improve cognitive performance in individuals living with schizophrenia under their usual antipsychotic medication by restoring neural synchrony and enhancing cortical connectivity. This will subsequently improve clinical and functional status and medication adherence.

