#### CBTp Intervention

Participants on both arms will receive CBTp in 16 individual-based, 50-minute-long, weekly sessions with 2 booster CBTp sessions (with active or sham tACS) at 1-month and 3-month follow-up visits (after intervention).

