### Statistical Outcomes

#### Primary Outcome Measures

EEG gamma oscillations are fast neural rhythms linked to higher-order cognitive functions (attention, working memory, executive control, and consciousness). In the prefrontal cortex, gamma EEG activity is associated with working memory maintenance, cognitive flexibility, top-down attention control, and integrating information across cortical areas. Altered prefrontal gamma observed in schizophrenia. EEG measurement of gamma activity in the prefrontal cortex refers to detecting brain oscillations in the gamma frequency band (typically 30-100 Hz, often subdivided into low gamma: 30-50 Hz, and high gamma: 60-100 Hz) from scalp electrodes positioned over prefrontal areas. In a within-subject design, we will compare gamma power across time windows (pre- and postintervention). In a between-subject design, we use mixed models or *t* tests on summary metrics (mean power in time×freq window).

PANSS is a standardized clinical interview that rates the presence and severity of positive and negative symptoms and general psychopathology for people with schizophrenia within the past week [32]. The scale consists of 30 items: 7 positive, 7 negative, and 16 general psychopathology symptoms. The symptom severity for each item is rated according to a 7-point scale (1=absent to 7=extreme) to best describe the symptom’s presentation. The clinical interview takes approximately 45 minutes. The patient is rated from 1 to 7 on 30 different symptoms based on the discussion and reports of family members or primary care hospital workers. As 1 is the lowest score for each item, a patient cannot score lower than 30 for the total PANSS score. Scores are often given separately for positive items, negative items, and general psychopathology. [Time frame: PANSS will be applied at visit 1, screening (week 0); visit 4, end of intervention (week 17); visit 5, follow-up 1 (week 21); and visit 6, follow-up 2 (week 29).]

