#### Secondary Outcome Measures

HRV refers to the variation in time between consecutive heartbeats, a normal physiological phenomenon indicating the body’s ability to adapt to stress and demands. There is no single “ideal” HRV; a higher HRV generally indicates better cardiovascular health and fitness, with a normal range considered to be between 40 and 100 milliseconds. HRV provides insights into the body’s autonomic nervous system balance and overall psychological health. It reflects the variations in time intervals between heartbeats, indicating how well the body adapts to stress and recovers. However, individual HRV levels vary based on age, fitness level, and other factors, and tracking baseline HRV and trends for an individual is more important than comparing to others. [Time frame: HRV will be determined at visit 2, week 1, before and immediately after the first intervention (tACS/CBTp); it will also be determined pre- and post-16th intervention, visit 4, week 17.]

The World Health Organization Disability Assessment Schedule 2.0 (WHODAS 2.0) measures the level of functioning in 6 domains of life [35,36]: cognition—understanding and communicating; mobility—moving and getting around; self-care—attending to one’s hygiene, dressing, eating, and staying alone; getting along—interacting with other people; life activities—domestic responsibilities, leisure, work, and school; participation—joining in community activities and participating in society. The 36-item WHODAS 2.0 is the most detailed version (questions about the difficulties experienced in the past 30 days). It allows users to generate scores for the 6 functioning domains and calculate an overall functioning score. The average interview time for the interviewer-administered 36-item version is 20 minutes. The simple sum of the scores of the items across all domains constitutes a statistic that describes the degree of functional limitations. The scores range from 0 to 100, where higher scores indicate greater disability. [Time frame: WHODAS 2.0 will be performed at visit 2, baseline (week 1); visit 4, end of intervention (week 17); visit 5, follow-up 1 (week 21); and visit 6, follow-up 2 (week 29).]

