## Results

### Duration of Participation

The timeline for recruitment, treatment, and follow-up is 18 months, followed by 6 months for data analysis, writing manuscripts, and dissemination activities.

Total duration of participation in this research will be 29 weeks; the visits, procedures, and timelines are represented in Table 2. In addition to the study visits, participants will be seen weekly for 16 weeks to receive CBTp with either tACS or sham tACS, and there will be a booster session intervention during each of the two follow-up visits.

**Table 2 table2:** Study calendar, visits, procedures, and timelines^a^.

Study phases	Phase I: Preintervention		Phase II: Intervention		Phase III: Postintervention	
Timeline	Visit 1	Visit 2	Visit 3	Visit 4	Visit 5	Visit 6
Procedure	Screening	Baseline	Session 8	Session 16	Follow-up	Follow-up
Duration	Week 0	Week 1	Week 9	Week 17	Week 21	Week 29
Informed consent, 60 minutes	✓					
Chart review, 60 minutes	✓					
Height and weight, 10 minutes	✓					
Vital signs, 15 minutes	✓	✓	✓	✓	✓	✓
Physical exam, 20 minutes	✓					
MoCA^b^/age >65 years, 20 minutes	✓					
C-SSRS^c^, 10 minutes	✓					
Bem Sex-Role Inventory, 15 minutes	✓					
Chart review, 30 minutes	✓					
Physical exam, 20 minutes	✓					
Vitals, 10 minutes	✓	✓	✓	✓	✓	✓
PANSS^d^, 40 minutes	✓			✓	✓	✓
NSA-16^e^, 15 minutes		✓		✓	✓	✓
WHODAS 2.0^f^, 10 minutes		✓		✓	✓	✓
CFS^g^ and PSS^h^, 10 minutes		✓	✓	✓	✓	✓
PETiT^i^, 10 minutes		✓	✓	✓	✓	✓
Q-LES-Q-SF^j^, 5 minutes		✓	✓	✓	✓	✓
BBTS^k^, 10 minutes		✓				
WAI-SR^l^, 5 minutes			✓	✓		
Stroop^m^, 10 minutes		✓		✓	✓	✓
EEG^n^, 30 minutes including prep.	✓			✓		
HRV^o^ (beginning and end of session), 5 minutes		✓		✓		

^a^Benzodiazepines and other medications for sleep or anxiety must be held for at least 8 hours before assessments. This questionnaire/assessment must be done at approximately the same time of day each time. If these cannot be done during a scheduled visit, the participant may be rescheduled for another day. Participants will be allowed to take short breaks during these assessments if they need them.

^b^MoCA: Montreal Cognitive Assessment.

^c^C-SSRS: Columbia Suicide Severity Rating Scale.

^d^PANSS: Positive and Negative Syndrome Scale.

^e^NSA-16: 16-item Negative Symptom Assessment.

^f^WHODAS 2.0: World Health Organization Disability Assessment Schedule 2.0.

^g^CFS: Cognitive Flexibility Scale.

^h^PSS: Perceived Stress Scale.

^i^PETiT: Personal Evaluation of Transitions in Treatment.

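### The abstract has EEG judging efficacy at both follow-ups although EEG is scheduled only at weeks 0 and 17, and the week 17 EEG is not fixed as before or after that visit's stimulation

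*Protocol article*

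**What the plan says.** The Methods part of the abstract lists "Primary outcome measures—electroencephalogram, Positive and Negative Syndrome Scale, 16-item Negative Symptom Assessment, and Cognitive Flexibility Scale" and says that these "will evaluate the efficacy of treatment at the end of the intervention and at the two follow-ups". EEG is named first of the four.

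Table 2 (Duration of Participation) has one EEG row, "EEG^n^, 30 minutes including prep", ticked at visit 1 (screening, week 0) and visit 4 (week 17). The cells for visits 5 and 6 are empty. PANSS, NSA-16 and CFS are ticked at both.

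Primary Outcome Measures describes the within-participant EEG analysis as "we will compare gamma power across time windows (pre- and postintervention"). It gives EEG no visit schedule, although PANSS, NSA-16 and CFS each have one. The Objectives section places the EEG expectation at the end of therapy.

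On stimulation at the assessment visits:

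- Table 2 heads visit 4 as session 16.
- The HRV time frame in Secondary Outcome Measures agrees: "it will also be determined pre- and post-16th intervention, visit 4, week 17".
- CBTp Intervention adds "2 booster CBTp sessions (with active or sham tACS) at 1-month and 3-month follow-up visits".
- The text before Table 2, however, describes the weekly sessions as additional to the study visits.

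Background and Scientific Rationale reports after-effects of tACS lasting "70 minutes after one stimulation session for 20 minutes".

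**The concern.** There are two linked problems with one primary outcome.

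First, the abstract and the calendar give incompatible EEG schedules. A reader of the abstract would expect EEG evidence of durability at weeks 21 and 29, and no such data will exist.

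Second, the stimulation is in the gamma band, the EEG outcome is prefrontal gamma power, and the article itself cites an after-effect of more than an hour. If the week 17 EEG is taken soon after session 16, the between-arm difference in gamma could partly reflect that day's stimulation and not only the 16-week course. The baseline EEG is at screening, with no stimulation, so a same-day effect would enter only the active arm's pre-post change and would not cancel.

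The sample size section says the pilot is meant to supply unbiased SDs and preliminary effect sizes for a definitive trial. A same-day component would shift the EEG effect size. A mixture of orders across participants would widen the SD. Both would pass into the next sample size calculation.

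**Working it through.** None of the plan's calculated figures bears on this point. Its one such figure, a detectable effect of about d = 1.1 with 14 per arm, reproduces as 1.100 (two-sample t test, assuming two-sided 5% and 80% power, which the article does not state). Nothing below depends on it.

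**Time points for EEG**

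- Promised after baseline (abstract): weeks 17, 21 and 29, so 3.
- Scheduled after baseline (Table 2): week 17, so 1.
- Missing: 3 − 1 = 2, which is both follow-ups.

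The Objectives, Primary Outcome Measures and Table 2 agree with one another. The abstract sentence is the outlier, and it fails for EEG only.

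**Timing at visit 4**, with the end of stimulation as minute 0

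- Session length 50 min, stimulation in the first 20 (tACS/Sham tACS; Table 1), so the session ends at minute 50 − 20 = 30.
- EEG slot: "30 minutes including prep". Straight after the session it runs from minute 30 to minute 30 + 30 = 60.
- Cited after-effect: up to minute 70. Since 60 < 70, the whole slot lies inside the window.
- To clear the window, the EEG must start at least 70 − 30 = 40 min after the session ends.

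**Other orders**

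- EEG before stimulation: no same-day after-effect.
- EEG after all other visit 4 assessments, if these follow the session. Table 2 durations, vitals counted once at 15 min: 15 + 40 (PANSS) + 15 (NSA-16) + 10 (WHODAS 2.0) + 10 (CFS and PSS) + 10 (PETiT) + 5 (Q-LES-Q-SF) + 5 (WAI-SR) + 10 (Stroop) + 5 (HRV) = 125 min. The EEG would start at about minute 30 + 125 = 155, outside the window.

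**Effect on the contrast**

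Let L be the lasting change in gamma, S the same-day effect of active stimulation, and p the share of active-arm participants whose EEG falls in the window. Take S as nil for sham, which Table 1 limits to a few seconds. Then

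active − sham change = (L_active − L_sham) + p × S.

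The extra term is 0 if every EEG precedes stimulation, and S if every EEG follows the session directly. For a constant S and order unrelated to L, a mixture of orders adds p(1 − p)S² to the active-arm variance. The documents give no value for S or p, so the bias cannot be sized in gamma units.

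**Does session 16 fall at visit 4?**

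The Table 2 heading and the HRV time frame say yes. Two points pull the other way. One is the statement that weekly sessions are additional to study visits. The other is the calendar: if session 1 is at visit 2 in week 1, as the HRV text has it, weekly sessions put session 8 in week 8 and session 16 in week 16, while Table 2 shows weeks 9 and 17. These passages must be reconciled.

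**The case against.** The strongest reply is that the order of procedures within a visit is operational detail, which a journal article may leave to the full protocol. Nothing in the article says the EEG follows stimulation, and two of the three orders above are harmless. Table 2's footnote also allows assessments to be moved to another day, and the wording about additional weekly sessions leaves some doubt that EEG and session 16 coincide. This stands to the extent that the same-day effect is a possibility and not a demonstrated defect. A reader might infer that the week 17 contrast does mix acute and lasting effects; the article does not support that.

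The 70-minute figure also needs care. The Background ties it to a resonance at the stimulated frequency, taken from a cited study, and does not name gamma. Applying it here is an assumption.

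A reader might extend the argument to every outcome collected at a session visit. The article gives no ground for that. PANSS and PETiT refer to the past week, PSS to the past month and WHODAS 2.0 to the past 30 days, and nothing suggests that 20 minutes of stimulation alters such ratings. The argument is plausible for EEG and, less directly, for performance tests such as Stroop.

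Finally, the pilot is declared unpowered for efficacy, its outcome analyses are described as descriptive, and the body makes no EEG durability claim. That limits the consequence but does not remove the contradiction. Nor does it excuse an avoidable bias in effect sizes meant for planning. The article does fix measurement order for HRV, and it sets a time-of-day rule and a medication hold for assessments, so stating the EEG order would be in keeping with its level of detail.

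**Conclusion.** The contradiction is established: EEG is promised at three post-baseline time points and scheduled at one. The EEG efficacy statement can cover week 17 only, and no claim of EEG durability is possible from the planned data.

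The timing point holds conditionally. If session 16 is at visit 4, if the EEG follows it directly, and if the cited 70-minute after-effect applies to this stimulation, the EEG falls at minutes 30 to 60 and the between-arm gamma contrast includes a same-day component absent from baseline. If the EEG precedes stimulation, or starts more than 70 minutes after it, this problem does not arise. The article does not settle which applies, and the size of any same-day component is unknown. No sample size figure changes.

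**What to change.** 1. Reword the abstract so that EEG evaluates efficacy at the end of the intervention (week 17) only, and make no statement on EEG durability. Adding EEG at visits 5 and 6 would raise the same order question, since boosters with active or sham tACS are given there.
2. Require the visit 4 EEG to be recorded before that day's stimulation. Preferably do the same for performance tests such as Stroop at any visit with a session.
3. Log clock times for the EEG and for the start and end of stimulation.
4. Report the order for participants already assessed. On 1 November 2025, 12 participants were following the protocol; the article does not say how many had reached visit 4.
5. Reconcile the session 16 heading and HRV time frame with the statement that weekly sessions are additional to study visits, and with the week numbering.

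Cost: wording, a visit-order instruction and two or three logged times, with no new procedure. Participants wait somewhat longer before the session, by the 30-minute EEG slot or by 40 minutes if Stroop (10 minutes) is moved too. If current practice has been to record EEG after the session, the change makes later participants differ from earlier ones, so the logged or reconstructed order should be shown with the EEG results.

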**Results:**

The timeline for recruitment, treatment, and follow-ups is 18 months, followed by 6 months for data analysis, writing manuscripts, and dissemination activities. By November 1, 2025, we have enrolled 15 participants: 12 are following the intervention protocol (8 active and 4 sham tACS). Two participants were screening failures, and one participant withdrew after intervention 2.

**Conclusions:**

Our expectations are as follows. CBTp will improve the scores of psychological and psychosocial tests at the end of therapy for both groups, but it will be superior for the group with tACS intervention. Considering that cognitive and emotional status is gender dependent (hormonal differences, brain structure, and sociocultural influences), we expect that the therapeutic response could be gender specific. CBTp will enhance electroencephalogram activity and the heart in clients with schizophrenia at the end of therapy for both groups, but it will be superior for the group with tACS preintervention. The baseline heart rate variability will predict symptom improvement and will increase over the course of therapy. We hope our research will improve the treatment of people living with schizophrenia, thereby enhancing their quality of life, reducing the rate of relapse, and lowering the costs of care.

**Trial Registration:**

ClinicalTrials.gov NCT06889025; https://clinicaltrials.gov/study/NCT06889025

**International Registered Report Identifier (IRRID):**

PRR1-10.2196/80593

## Introduction

### Background and Scientific Rationale

Schizophrenia is a debilitating neurodevelopmental disorder with tremendous consequences for the individual and family, resulting in an important socioeconomic burden. There are approximately 360,000 people affected by schizophrenia in Canada. The illness usually begins between the ages of 15 and 35 years, during key developmental milestones of life. Ontario has the largest number of individuals living with schizophrenia; 84,000 Ontarians (and their families) are affected by treatment-resistant schizophrenia.

The mainstay treatment of schizophrenia is antipsychotic medication. However, antipsychotics do not work adequately for up to 60% of individuals [1]. Although evidence shows that medication has beneficial effects on positive symptoms (hallucinations, delusions, etc) and reduces relapses, a significant number of patients do not fully respond to it [2]. The persistence of symptoms throughout its evolution, compounded by the added side effects of medication, leads to significant impairments in social and relational aspects of life, contributing to the significant distress and disability associated with the disorder. Combined, early medical and psychosocial interventions are consistently sought, while research explores new avenues to enhance current approaches or attempt stand-alone, successful, cost-effective, and noninvasive treatments [3]. When cognitive behavioral therapy for psychosis (CBTp) is used alongside medication, some improvements have been observed. Still, the debilitating negative symptoms remain (such as reduction of emotional expression, lack of social involvement, inability to initiate goal-directed activities, etc), which are key factors in long-term disability [4,5].

Schizophrenia is characterized by abnormalities in neural circuitries resulting in dysfunctional cognition and behavior [6,7]. A new treatment, transcranial alternating current stimulation (tACS), has therapeutic results in Alzheimer disease [8-10]. Recent randomized double-blind clinical trials of tACS in Alzheimer disease showed a significant improvement in memory performance, along with restoration of intracortical connectivity, as compared to sham tACS [11-13]. Recent systematic reviews discuss the general optimism within the scientific community regarding the use of electrical currents in enhancing cognitive performance in healthy people and ameliorating symptoms in a wide variety of conditions, including neuropsychiatric ones [6,14-16]. The rationale behind such an approach rests on the understanding that neural oscillations are a fundamental mechanism that organizes the temporal relationship of activity patterns in brain networks [2,17,18]. Certain psychiatric disorders were identified over the last decades as showing imbalances in network connectivity, showing high or slow oscillatory activity by comparison with the healthy population. If tACS improves memory in Alzheimer disease by modulating brain oscillations, then it may also enhance cognitive function in schizophrenia by targeting similar neural mechanisms, particularly those involving working memory and gamma oscillations. Of note, gamma synchrony stands out as a binding mechanism for integrating disparate brain networks, mediating perception, cognition, and memory [3], which is typically disturbed in schizophrenia. Manifesting as synchronous high-frequency oscillations of brain electrical activity, it occurs across several brain regions whose functions are integrated this way [19,20]. Global delays and decreased temporal connectivity in neural activity stemming from impairments in frontal lobe synchrony may be relevant to the disordered cognitive control and flexibility in schizophrenia [21-23].

tACS, the focus of our study, applies a low-intensity sinusoidal electrical current to the brain through electrodes placed on the scalp, and it is thought to boost the brain’s own oscillation by way of entrainment. When a single frequency is applied, this exogenous oscillation will synchronize with the brain’s endogenous frequency. Conversely, multiple frequencies lead to desynchronization of cortical oscillations [24]. The value of the frequency applied thus becomes a determining factor in the effects sought and identified in tACS studies.

Research focusing on tACS mechanisms has shown that effects result from manipulating the membrane potential of neurons that are aligned with the introduced electric field, mostly pyramidal cells in layer V [25,26]. Upon stimulation by tACS, which will cause an alternating change in membrane potential, these cells demonstrate a resonance specific to the frequency of stimulation, with long-term aftereffects—70 minutes after one stimulation session for 20 minutes [19]—and implications on oscillatory cortical connectivity between different cortical regions [27]. In auditory hallucinations, research has demonstrated interhemispheric miscommunication, where tACS can manipulate auditory perception in healthy participants by decoupling this interhemispheric connectivity [28]. The advantage of using tACS over other noninvasive brain stimulation modalities lies in its effectiveness in entraining endogenous brain oscillations, as it mimics the alternating nature of these oscillations [29,30].

From a practical standpoint, tACS exhibits superior cost, portability, tolerability, and safety profiles [17]. tACS is a feasible tool that reshapes or resynchronizes intrinsic brain rhythms, manipulating the associated brain functions without adding extra excitatory or inhibitory burden.

We hypothesize that tACS targeting gamma oscillations, added to each CBTp session, will improve cognitive performance in individuals living with schizophrenia under their usual antipsychotic medication by restoring neural synchrony and enhancing cortical connectivity. This will subsequently improve clinical and functional status and medication adherence.

